#### Parenting outcomes

We will measure women’s readiness for baby care using an item designed by Ickovics et al. [17]. Women’s self-efficacy in child care will be evaluated using the Parental Expectations Survey (PES) [55].

#### Satisfaction with prenatal care

Women’s experience and satisfaction with prenatal care will be evaluated using the Patient Participation and Satisfaction Questionnaire (PPSQ) [56, 57].

#### Process outcomes

We will assess the implementation of CP by monitoring the percentage of women that start CP, the addressed content within the group sessions, the involvement of women and their partners (adherence), and model fidelity. These data will be collected from the CP-group-evaluations, filled out by the group facilitators at the end of each session. These evaluations also contain data on group cohesion. Women’s experience with CP and their inhibiting and facilitating factors to participate will be addressed in the self-administered questionnaires: see Table 1. Inhibiting and facilitating factors in the implementation process and the care providers satisfaction with prenatal care will be addressed in individual semi-structured in-depth interviews. Health care utilization of women will be measured in the self-administered questionnaires, addressing preconceptional and prenatal utilization of general health care, and health care utilization provided by a perinatal care center.

### Statistical issues

#### Sample size calculation

A minimal sample of 600 pregnant women in both the intervention and control condition is needed to be able to accept with 95% confidence and an upper confidence limit less than 1.85, that after the intervention has been implemented, there is at least no significant difference in infant morbidity (using 14% of infant morbidity as outcome) between CP and individual care. This sample size is also largely sufficient to find amongst others a difference in prenatal care satisfaction or in proportion of breastfeeding comparable to Ickovics et al, with an α of 0.05 and a power of 0.90 [17]. We will account for a 20% loss to follow-up and aim to include in total 1600 women (800 in both conditions).

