## Methods

### Design

This study will be performed in thirteen midwifery practices (primary care, low-risk population) and two hospitals (secondary care, moderate to high-risk population) that do not yet offer CenteringPregnancy within the region ‘northern South-Holland’ (an urban – sub-urban setting). A stepped wedge cluster randomized controlled trial design is chosen for several reasons. Firstly, randomization at individual level is not appropriate, as training professionals in CP will most probably also affect the non-CP consultations. Secondly, since midwifery care in the Netherlands is subjected to marketing forces, cluster randomization is expected to result in unfair competition between independent centers operating in the same region. Within the chosen design, all clusters (midwifery practice or hospital) start to collect control data at the same time (control period). Clusters will subsequently implement the intervention at a different, randomly selected time point and will then start to collect intervention data (intervention period). For this study, we will divide all fifteen centers into three groups and will randomly assign each group to one of three time points (steps) at which they will start to implement the intervention, with a between-step period of 3 months.

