#### Data analysis

Data entry will be automatic by using a secured online survey system or (in case of hard copy) scanned and checked using the Teleform software. Data will be stored in a digital data base only accessible to the researchers. Before analysis, all data will be cleaned improving data quality.

We will conduct intention-to-treat analyses to compare the primary and secondary outcomes of the control group with those of the complete intervention group. Also a per protocol analysis will be performed comparing the outcomes of the three subgroups (see Fig. 1): control group (1), CP-participants (2) and non-CP-participants (3). Analyses will be descriptive and inferential (univariate and multivariate), and we plan to perform multilevel techniques to account for the clustering effect among participants in centers and CP-participants in CP-groups. The analysis of the implementation data and health care use will be descriptive. The relation between the degree of implementation and primary and secondary outcomes will be analyzed using multi-level analysis. Furthermore, the interviews with care providers will be conducted using a topic list based on the results of the analysis of the implementation data. They will be transcribed and qualitatively analyzed using a framework approach.

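### The sample size of 600 per condition shows no allowance for the stepped-wedge clustered design, so its adequacy is not demonstrated

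*Protocol article*

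**What the plan says.** The Sample size calculation section of the protocol article opens with "A minimal sample of 600 pregnant women in both the intervention and control condition is needed to be able to accept with 95% confidence" and derives that number from three inputs: "95% confidence and an upper confidence limit less than 1.85", a rate given as "using 14% of infant morbidity as outcome", and a target of no significant difference between the two care models. It does not say whether 1.85 is an odds ratio or a risk ratio, and it gives no power for this target.

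It then adds: "This sample size is also largely sufficient to find amongst others a difference in prenatal care satisfaction or in proportion of breastfeeding", of the size seen in a cited earlier trial, "with an α of 0.05 and a power of 0.90". Those effect sizes are not reproduced. The last step allows for 20% loss and arrives at 800 per condition, 1600 in total.

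The Design section describes a different structure from two independent samples. Fifteen centres are split into three groups, and the trial will "randomly assign each group to one of three time points (steps) at which they will start to implement the intervention", with three months between steps. In the Data analysis section, "we plan to perform multilevel techniques to account for the clustering effect among participants in centers and CP-participants in CP-groups". The Discussion counts the ability to take time effects into account among the design's strengths.

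**The concern.** The chain from inputs to 1600 is given in full, and no link in it refers to centres, care groups, steps or calendar time. The design makes these matter. Every centre moves from control to intervention, so intervention data are later by construction. An unadjusted comparison confounds the intervention with time; an adjusted one must rely on the part of the data in which some centres have crossed over and others have not.

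This is more than a detail left to a fuller document, because the section asserts that 600 is enough, and that assertion can be tested against the design in the same article. At stake is whether the trial can meet its own criterion for infant morbidity, and whether the claim of ample power for satisfaction and breastfeeding can be relied on.

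**Working it through.** **Inputs from the article.** 600 per condition, limit 1.85, rate p = 0.14, 20% loss, 1600 in total, 15 centres, 3 sequences.

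**Assumptions.** Five equal-sized centres per sequence; four recruitment periods; fixed period effects and a random centre effect; ICC 0 to 0.05; no true difference. Clustering within care groups is left out.

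**Step 1: can 600 be reproduced?** For independent women, n per condition = f × (1.96 + z)² / (ln 1.85)², where z is the normal quantile for the chosen power and ln 1.85 = 0.615. On the odds-ratio scale f = 2/(0.14 × 0.86) = 16.61; on the risk-ratio scale f = 2 × 0.86/0.14 = 12.29.

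| Power | Odds ratio | Risk ratio |
|---|---|---|
| 80% | 345 | 255 |
| 90% | 462 | 342 |
| 95% | 571 | 422 |
| 99% | – | 597 |

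Only a risk ratio with an unstated 99% power comes close to 600, so the formula behind it can only be inferred. Taking 600 as given, SE = √(16.61/600) = 0.166 and the chance of meeting the limit is Φ(0.615/0.166 − 1.96) = 0.96. On the risk-ratio scale SE = √(12.29/600) = 0.143 and the chance is 0.99.

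**Step 2: loss to follow-up.** 600/0.8 = 750, so 800 is not short; it leaves 800 × 0.8 = 640.

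**Step 3: cost of adjusting for period.** With four equal periods the share of centres in intervention is 0, 1/3, 2/3 and 1. The within-period variance of the treatment indicator is 0, 2/9, 2/9 and 0, with mean 1/9. Two concurrent equal arms give 1/4. At ICC 0 the design effect is therefore (1/4)/(1/9) = 2.25.

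**Step 4: adding centre clustering.** The Hussey–Hughes variance, divided by the variance for independent women, with 1200 analysed gives 2.68 at ICC 0.01, 2.87 at 0.02 and 3.07 at 0.05. Without period terms the same model gives only 1.00 to 1.10, so most of the loss comes from period adjustment.

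**Step 5: consequence for the 1.85 criterion.** Each SE is multiplied by the square root of the design effect. For example, at ICC 0 and 1200 women, 0.166 × √2.25 = 0.250 and Φ(0.615/0.250 − 1.96) is about 0.69. The expected upper limit is exp(1.96 × SE). Equal periods, ICC 0 to 0.05:

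| Analysed | Chance, odds ratio | Chance, risk ratio | Expected limit, odds ratio |
|---|---|---|---|
| 1200 | 0.69–0.56 | 0.82–0.69 | 1.63–1.77 |
| 1600 | 0.81–0.67 | 0.91–0.80 | 1.53–1.65 |

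In effective numbers, 600/2.25 = 267 and 600/3.07 = 195 per condition. Both are below the 345 needed on the odds-ratio scale for 80% power.

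**Step 6: longer first and last periods (assumed).** With periods of 6/3/3/6 months and 1200 analysed, the design effect is 3.4–4.0 and the expected odds-ratio limit 1.82–1.92. With 9/3/3/9 months these become 4.5–5.0 and 2.0–2.1. If 35% of recruitment falls in each of the first and last periods and 15% in each middle one, the limit is 1.88–1.97 with 1200 analysed but 1.73–1.81 with 1600.

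**Step 7: the 0.90 power.** If 600 were exactly the independent-women requirement, power would become Φ(3.24/√D − 1.96), where D is the design effect: 0.58 at D = 2.25 and 0.46 at D = 3.07. For 0.90 to hold, that requirement would have to be no more than about 267 to 195 per condition.

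**The case against.** A reader might infer that the calculation demonstrably treats women as independent, and that the stated precision and the 0.90 power will not be delivered. The documents do not support that.

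- No formula, scale or primary power is given. Against conventional 80–90% power, 600 is 1.3 to 2.35 times the independent-women requirement (600/462 to 600/255). This slack is unexplained and mostly smaller than the design effect, but it rules out calling the figure an arithmetic error.
- No probability of meeting the limit is claimed, and with equal periods the expected limit stays below 1.85. What falls is the chance of achieving it.
- The 0.90 applies only to satisfaction and breastfeeding. Their effect sizes are not in the article, and 600 is described as more than enough for them. The fall to 0.46–0.58 is conditional, not established.
- The primary outcomes come from a registry and the questionnaires are optional, so more than 1200 women may be analysed. The more favourable 1600 figures belong beside the 1200 figures.
- The Data analysis section commits to multilevel modelling, not explicitly to period terms, and centre clustering alone costs little.
- A neutral result need not be over-read: a correctly computed wide interval would miss the 1.85 criterion and be inconclusive.

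All of this stands and limits the claim. It does not remove it. Period effects are needed in this design, and the Discussion presents handling them as a strength. The slack does not cover the cost on the odds-ratio scale at 1200 women. Unequal centres (13 practices and 2 hospitals) and clustering within care groups would generally add to the loss.

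**Conclusion.** The point holds as a mismatch between a stated adequacy claim and the trial's own design. With four equal periods, 15 equal centres and period effects fitted, the design effect is 2.25 at ICC 0, a figure that needs no assumed clustering, and about 2.7–3.1 at ICC 0.01–0.05. The chance of satisfying the 1.85 limit then depends heavily on choices the article leaves open: across both ratio scales and 1200 to 1600 women analysed, it runs from 0.56 to 0.91. Longer first and last periods lower it further and can push the expected limit past 1.85. For satisfaction and breastfeeding, 0.90 power is not shown to hold; nor is it shown to fail. The ICC, period lengths and equal centre sizes are assumptions, because the article gives only the three-month spacing of the steps.

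**What to change.** Keep the target of 1600 women and restate the calculation:

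- Name the ratio scale of the 1.85 limit and the power intended for infant morbidity.
- Use the stepped-wedge variance with 15 centres, 3 sequences, the actual period lengths and fixed period effects, over a stated ICC range.
- Report the resulting precision or minimum detectable effect for infant morbidity, satisfaction and breastfeeding, with the number expected to be analysed for each.
- Keep the 0.90 power statement if that calculation supports it, giving the effect sizes used; otherwise restate it.

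The cost is one calculation, revised wording and less favourable stated figures. No additional women are required.

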Research on CP has shown some positive effects: amongst others on health literacy [25, 26], preparedness for labor and birth [17], and initiating breastfeeding [17, 27]. Women reported receiving more social support [28, 29], and were more satisfied with provided care [17, 28–30]. Moreover, the number of preterm births significantly decreased in a high-risk population, the mean birth weight increased and the number of women who received substandard care was reduced [17, 29].

However, a part of the evidence is derived from non-randomized studies. The evidence from randomized controlled trials (RCT) is less obvious, which is due to the limited number of RCT’s on prenatal group-based care and the variation in the reported outcomes [17, 27, 30, 31]. Recently, Caitlin et al. concluded that additional research is required to assess the effects of prenatal group-based care models, such as CP, on neonatal and maternal outcomes [26]. Furthermore, most results of the effect of CP originate from experimental studies conducted in high-risk populations and in the USA [17, 29, 31–34]. It is unknown what the effect of CP is in a different maternity healthcare system and in the general population.

The aim of the present study is to evaluate the effects of CP in the Netherlands in primary health care (low risk population) as well as in hospital based care (moderate to high risk population) on neonatal and maternal health outcomes, health behaviors and psychosocial outcomes. The effectiveness of CP will be established by comparing the outcomes in the intervention group (prenatal care within the CP model) and the control group (usual individual care). Primary hypotheses are that in comparison to the control group, the intervention condition will lead to better neonatal and maternal outcomes. Secondary hypotheses are that the effect on the outcome variables is mediated by (changes in) health literacy, self-regulation, health behavior, health care utilization as well as level of group cohesion and level of implementation.

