#### Neonatal health outcomes

The primary neonatal outcomes are perinatal mortality (defined as death per 1000 still- and life births from a GA above 22 weeks to 7 days postpartum) and perinatal morbidity. Perinatal morbidity (composite outcome) is defined as presence of congenital abnormalities, small for gestational age (birth weight below 10^th^ percentile), preterm birth (<37 weeks of GA), Apgar score after 5 min < 7 and/or admission to a neonatal intensive-care unit (immediately after birth). These outcomes will be retrieved from the Perined database, as well as gestational age at birth and birth weight. Other neonatal outcomes that will be addressed in the self-administered questionnaires are child’s crying- and sleeping behavior per 24 h (and to what extent women’s expectations on crying behavior are met), consultations with a general practitioner and/or pediatrician and admission to the hospital within 6 weeks postpartum.

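### The hypothesis is superiority, but the sample size rests on accepting no significant difference in infant morbidity, with no detectable effect or power given for the benefit

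*Protocol article*

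**What the plan says.** The Background section sets the direction of the trial: "Primary hypotheses are that in comparison to the control group, the intervention condition will lead to better neonatal and maternal outcomes". The main neonatal outcome that can be sized is a binary composite: "Perinatal morbidity (composite outcome) is defined as presence of congenital abnormalities, small for gestational age", together with preterm birth, low Apgar score and neonatal intensive-care admission.

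The section Sample size calculation begins "A minimal sample of 600 pregnant women in both the intervention and control condition is needed", and gives as the reason the wish to accept, at the 95% confidence level and with "an upper confidence limit less than 1.85, that after the intervention has been implemented, there is at least no significant difference in infant morbidity", using a 14% morbidity rate. The section's only pair of significance level and power (0.05 and 0.90) belongs to satisfaction with prenatal care and breastfeeding, which are not primary outcomes.

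Under Data analysis, the intention-to-treat analysis is to "compare the primary and secondary outcomes of the control group with those of the complete intervention group". By the section Intervention group, that group includes women recruited in the intervention period who chose individual care. A per-protocol comparison of controls, CenteringPregnancy (CP) participants and non-participants is planned alongside it. No non-inferiority test is named.

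**The concern.** The hypothesis and the sample size serve different objectives. A superiority hypothesis calls for a target reduction and the power to detect it, and neither is given for infant morbidity. What is given is a rule for accepting that there is no significant difference, bounded by a limit of 1.85 whose scale is not stated.

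The rule is itself unsound. Failure to reach significance is not evidence of equality, and an upper limit of 1.85 on a 14% base is far from no difference. Two consequences follow:

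- A neutral trial could be reported as having met its design goal while the data remain compatible with a sizeable excess of infant morbidity.
- A reader cannot tell what benefit the trial had a fair chance of showing.

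There is also some looseness about the contrast. The sizing sentence describes the comparison as group care against individual care, whereas the intention-to-treat comparison puts women who declined group care into the intervention arm. Including them pulls the comparison towards no difference, which favours the very conclusion the sizing sentence wants to accept.

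**Working it through.** **Inputs from the protocol article.** n = 600 per condition, control risk 14%, upper confidence limit 1.85, 95% confidence (sample size section); superiority hypothesis (Background); fifteen centres (Design). **Assumed here:** a two-sided 95% interval, independent women unless stated, and the reductions examined, because the article gives none.

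**1. Can 600 be reproduced?** Not uniquely, because power, scale, sidedness and assumed true effect are not stated. Four readings:

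| Reading | n per arm |
|---|---|
| Exclude odds ratio 1.85, true odds ratio 1, one-sided 0.025: n = 2(1.96 + z)² / [0.14 × 0.86 × (ln 1.85)²] | 345, 461, 570 for 80%, 90%, 95% power |
| Same on the risk-ratio scale, 99% power | 596 |
| Largest non-significant odds ratio still has an upper limit of 1.85 | 611 |
| Superiority, 14% against 8.1% (odds ratio 1/1.85), 90% power | 589 |

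The last three lie within 3% of 600, but they answer different questions and the text identifies none of them.

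**2. What does 1.85 tolerate?**
- As an odds ratio: odds 0.14/0.86 × 1.85 = 0.301, so risk 0.301/1.301 = 23.1%.
- As a risk ratio: 0.14 × 1.85 = 25.9%.

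**3. Which observed result meets both halves of the criterion** (not significant, and upper limit below 1.85)? Take 84/600 (14%) against 108/600 (18%).
- Odds ratio = (108/492)/(84/516) = 1.348, log 0.2989.
- SE = √(1/84 + 1/516 + 1/108 + 1/492) = 0.1585.
- 95% CI = exp(0.2989 ± 1.96 × 0.1585) = 0.99 to 1.84. Both halves are met.
- On the risk-ratio scale the same data give 1.29 (0.99 to 1.67), which also meets both.
- This is about the edge. With 109 events the odds-ratio upper limit is 1.86 and fails, while the risk ratio 1.30 just passes. With 110 events the risk-ratio interval is 1.01 to 1.70, so the result is significant and fails.

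**4. How often would real harm pass?** Suppose true risks of 14% and 18.2% (risk ratio 1.3). Summing the two binomial distributions over all results that meet both halves gives about 47% if 1.85 is an odds ratio and about 49% if it is a risk ratio.

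**5. Power for the stated hypothesis.** Two-sided 0.05, with p̄ the mean of the two risks:

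power = Φ{[√600 × |p₁ − p₂| − 1.96 × √(2p̄(1 − p̄))] / √(p₁(1 − p₁) + p₂(1 − p₂))}

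For a 20% reduction: (24.495 × 0.028 − 1.96 × 0.4693)/0.4689 = −0.499, so the power is 31%.

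| Relative reduction | Risk | Power, no clustering |
|---|---|---|
| 20% | 14% to 11.2% | 31% |
| 25% | 14% to 10.5% | 46% |
| 30% | 14% to 9.8% | 61% |
| 37% (risk ratio 0.63) | 14% to about 8.9% | 80% |

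**6. Effect of clustering (illustration only).** Take 600/15 = 40 women per centre and condition, and an assumed intracluster correlation of 0.01 to 0.05. The simple inflation 1 + 39 × ICC is 1.39 to 2.95, and power for a 30% reduction falls from 61% to 48% and 26%. This is not a full stepped-wedge calculation, and the article gives no correlation. It shows only the direction and the possible scale.

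**The case against.** The strongest reply has five parts.

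- **The trial is not disabled.** A reader might infer that the trial can neither test its hypothesis nor support any no-harm statement. The documents do not support that. The Data analysis section plans inferential comparison of the primary outcomes, so a superiority test can be run. With no true difference and no clustering, SE = √(2/(600 × 0.14 × 0.86)) = 0.1664, so 600 per arm would exclude an odds ratio of 1.85 with power Φ(0.615/0.1664 − 1.96), about 96%. Equal observed arms would give an upper limit of exp(1.96 × 0.1664) = 1.39. This stands: the defect lies in the stated objective and criterion, not in what the data could show.
- **The criterion has two halves.** A reader might infer that 14% against 20% would pass if 1.85 is a risk ratio (1.43, 95% CI 1.11 to 1.84). It would not, because that result is significant. Likewise, 23.1% and 25.9% are values of the bound, not results that would be reported as no difference. This stands, and it is why step 3 applies both halves. An excess of 18% over 14% still passes.
- **600 is not shown to be wrong.** This stands. Several readings come close, and none is identified by the text.
- **Dilution is partly addressed.** A per-protocol comparison is planned, the Discussion acknowledges selection bias and plans adjustment, and the sizing sentence also speaks of the intervention and control conditions, which fits the intention-to-treat contrast. This largely stands, and leaves only a need to name the contrast consistently.
- **The article is condensed.** The scale and the justification of 1.85 may appear in a fuller document. That may excuse their absence here. It does not excuse a printed rationale that serves a different objective from the printed hypothesis, or wording that treats non-significance as something to accept.

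**Conclusion.** The point holds. The hypothesis that "the intervention condition will lead to better neonatal and maternal outcomes" is a superiority claim, whereas the sample size for infant morbidity is justified by a no-difference criterion that would be met by 18% morbidity against 14%. A true risk ratio of 1.3 would meet it about half the time on either scale. No power is given for the hypothesised benefit. Before clustering, that power reaches 80% only for a fall of about 37% in relative terms, and is 61% or less for reductions of up to 30%. Clustering lowers these figures by an amount the article does not let one fix.

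The figures rest on the article's 14% and 600 per condition, on independent women and on two-sided 95% intervals. The mismatch itself does not depend on any assumption about correlation or uptake of group care. It should be corrected, because a neutral result could otherwise be presented as the outcome the trial was designed to show.

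**What to change.** Align the sample size section with the Background section:

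1. Name superiority of the intention-to-treat contrast (intervention period against control period) on infant morbidity as the objective.
2. Replace the 1.85 sentence with the reduction that 600 per condition can detect, giving significance level, power and a variance adjusted for the stepped-wedge design.
3. Delete the wording about accepting no significant difference, and report a neutral result as an estimate with its confidence interval.
4. If a no-harm statement is wanted, make it a named secondary non-inferiority analysis with the effect scale fixed and the margin justified. Use the planned per-protocol comparison as supportive only, because participants in group care are self-selected.

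The cost is a change of wording in the protocol and analysis plan. The stated figures become less favourable; no extra patients are needed.
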